
### Exposures, outcomes, and covariates

#### Exposure

Preoperative frailty in geriatric patients.Outcomes of patients followed up 30 days after surgery.

#### Outcomes

**Primary outcome**

Incidence of MINS. MINS is defined as a peak plasma cTnT concentration of 0.03 ng/mL or greater that is judged to be secondary to myocardial ischaemia (i.e., no evidence of a nonischaemic aetiology causing cTnT elevation, such as sepsis, pulmonary embolism, or myocarditis), which occurs during or within 30 days after surgery. Competent physicians should be informed to further check for ischaemic symptoms, such as myocardial ischaemic symptoms and ECG changes (Supplemental Appendix 1) [13, 30]. Blood samples will be collected before surgery and on the 1st, 2nd and 3rd days after the operation. If a patient has ischaemic symptoms within 30 days after surgery, the researchers will collect blood samples again (Table 2).

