**Methods and analysis:**

This prospective, multicentre, real-world observational cohort study will be conducted at 18 designated centres in China from January 2023 to December 2024, with an anticipated sample size of 856 patients aged 65 years and older who are scheduled to undergo noncardiac surgery. The primary outcome will be the incidence of MINS. MINS is defined as a fourth-generation plasma cardiac troponin T (cTnT) concentration ≥ 0.03 ng/mL exhibited at least once within 30 days after surgery, with or without symptoms of myocardial ischaemia. All data will be collected via electronic data acquisition.

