## Introduction

The ageing population is quickly increasing worldwide, with the number of people aged 65 years and older expected to reach 2 billion by 2050 [1, 2]. The number of geriatric people undergoing surgery over the past 20 years has increased faster than the ageing of the population [3], which has profound implications for the planning and delivery of health and social care. Clinical frailty is the most troubling manifestation of ageing; it is described as a state of increased vulnerability to poor resolution of homeostasis after a stressful event and is the result of a cumulative decline in multiple physiological systems over a lifetime [1, 2]. Many studies have described the prevalence of frailty, and different surgical specialties have different prevalences of frailty. In patients receiving elective orthopaedic surgery, the prevalence of frailty was 23%, whereas in patients undergoing emergency hip fracture surgery, it was 53% [4, 5]. Taking cancer surgery into account, studies have reported that the prevalence of frailty is 25% in patients who undergo elective cystectomy and 39% in patients who undergo emergency general surgery, with the basal lesion usually being a tumour [6, 7]. In vascular surgery, the risk of aortic aneurysm and peripheral artery disease increases with age, and an estimated 52% of patients undergoing elective vascular surgery are frail [8]. Research on rehabilitation and related outcomes has focused on frail geriatric patients during the perioperative period. Frailty is related to adverse perioperative outcomes [9, 10].

In addition to the underlying conditions of sepsis, pulmonary embolism and arrhythmias, MINS is defined as an increase in cardiac troponin (cTn) during noncardiac surgery or within 30 days, with or without ischaemia-related symptoms and signs or myocardial ischaemic changes (with or without necrosis) [11]. Myocardial injury and infarction are considered the leading causes of death after surgery and account for 25% of all postoperative mortalities [12, 13]; ischaemic myocardial injury occurring after surgery but not meeting the criteria for myocardial infarction is more common [14, 15].

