Frail populations often have a greater incidence of subclinical changes in cardiac structure and function, which are considered risk factors for the development of cardiovascular diseases (such as hypertension, heart failure and ischaemic heart disease) [16–19]. Many studies have focused on the development of MINS during the perioperative period, and retrospective studies involving adults aged 45 years and older are common. There is currently no pertinent research on the features, risk factors, or 30-day outcomes of MINS in frail geriatric patients. It is urgent to preoperatively assess the comprehensive health status of frail geriatric patients and to reverse or alleviate frailty as soon as possible [20]. Therefore, the main objective of this study will be to investigate the relationship between preoperative frailty and MINS in geriatric patients.

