#### Exclusion criteria

Refusal to provide signed informed consent;Expected length of hospital stay < 3 days;High perioperative troponin levels due to nonischaemic causes (e.g., sepsis, pulmonary embolism, arrhythmia);The same patient can only be included once, regardless of whether the reason for the second operation is related to the first cause.

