### Study implementation

Before the study begins, each member of the research team will receive thorough instruction on how to correctly administer the MMSE, aCCI, mFI, BI, EQ-5D-3 L, and QoR15. Participants will only be allowed to participate after passing the test. (Supplemental Appendix 1)

**Mini-Mental State Exam (MMSE)**. This scale is simple, widely used and the first choice for dementia screening. Time orientation, place orientation, immediate memory, attention and calculation, delayed memory, language, and visual space are the seven components of the scale. There are a total of 30 questions; 1 point is awarded for each correct response, 0 points for a bad response or no response, and the scale’s overall score range is 0 to 30. The test results and educational level are closely associated. Unliterate > 17 points, primary school > 20 points, and junior high and above > 24 points are the typical cut-offs.**Age-adjusted Charlson Comorbidity Index (aCCI)**. The ACCI is a more widely used scoring system for complications than the CCI is. Complications are quantified based on the number and severity of patients’ diseases and can be used to predict the risk of disease-related death [24].**Assessment of activities of daily living**. The patients will be assessed preoperatively using the Barthel index (BI) evaluation form; 0–40 is classified as severe dysfunction, 41–60 is classified as moderate dysfunction, 61–99 is classified as mild dysfunction, and 100 is classified as self-care.**Preoperative frailty assessment** The mFI is an NSQIP-based 11-factor index that has been shown to adequately reflect frailty and predict mortality and morbidity. The mFI is calculated by dividing the number of factors present in a patient by the number of available factors for which there are no missing data. An mFI score of 0 is classified as healthy, 0-0.21 is classified as prefrail, and ≥ 0.21 is classified as prefrail. The index includes 11 items: nonindependent function or activity status, history of diabetes, history of chronic obstructive pulmonary disease (COPD) or pneumonia, history of congestive heart failure, history of myocardial infarction, angina pectoris, percutaneous coronary intervention (PCI), cardiac surgery, hypertension requiring medication, peripheral vascular disease or static pain, sensory disturbance, transient ischaemic attack (TIA) attack or cerebrovascular accident without sequelae, and cerebrovascular accident with sequelae [25]. In this study, patients with moderate or severe dysfunction and a BI ≤ 60 will be considered positive for item 1.**European Five-dimensional Three-level Quality of Life Scale (EQ-5D-3 L)**. The EQ-5D scale consists of two parts: the EQ-5D-3 L health description system and the EQ-VAS. The EQ-5D-3 L health description system describes five dimensions: mobility, self-care, usual activities, pain/comfort, and anxiety/depression. Each dimension contains three levels. The EQ-VAS records the interviewees’ self-assessed health status on a vertical visual analogue scale, and the two ends of the scale are marked with “the best health status in your imagination” and “the worst health status in your imagination”. The EQ-VAS provides a quantitative description of respondents’ perceptions of their overall health [26].**Diagnostic criteria of MINS**. During noncardiac surgery or within 30 days after surgery, the postoperative troponin level is increased due to myocardial ischaemia (i.e., there is no evidence of nonischaemic causes), and there is no requirement for ischaemic characteristics (such as ischaemic symptoms and ischaemic ECG findings) [27].Quality of Recovery-15 (QoR-15**)**. The QoR-15 is a patient-reported outcome measurement validated to measure the QoR after surgery and general anaesthesia. The BDI ranges from 0 to 150, with a higher score indicating better recovery [28]. The QoR-15 is a smaller version of the QoR-40; the psychometric properties are comparable, but the QoR-15 is more practical to use because it is shorter and takes less time to complete [28, 29]. The following QoR scoring criteria will be used: excellent (QoR-15 > 135), good (122 ≤ QoR-15 ≤ 135), moderate (90 ≤ QoR-15 ≤ 121) or poor (QoR-15 **<** 90).

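### MINS is fixed as an absolute cTnT threshold with no stated use of the preoperative value, so an unchanged preoperative elevation can count as an event, possibly more often in frail patients

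*Protocol article*

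**What the plan says.** The Protocol article words the outcome in four places.

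- **Primary outcome:** "MINS is defined as a peak plasma cTnT concentration of 0.03 ng/mL or greater that is judged to be secondary to myocardial ischaemia". Ischaemic origin is inferred from the absence of another cause: "no evidence of a nonischaemic aetiology causing cTnT elevation, such as sepsis, pulmonary embolism, or myocarditis". The event must occur during surgery or in the 30 days after it.
- **Abstract, Methods and analysis:** a cTnT of at least 0.03 ng/mL "exhibited at least once within 30 days after surgery, with or without symptoms of myocardial ischaemia". No judgement of ischaemic origin is mentioned.
- **Introduction:** "MINS is defined as an increase in cardiac troponin (cTn) during noncardiac surgery or within 30 days".
- **Study implementation, diagnostic criteria:** "the postoperative troponin level is increased due to myocardial ischaemia (i.e., there is no evidence of nonischaemic causes".

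On sampling, the Primary outcome section says: "Blood samples will be collected before surgery and on the 1st, 2nd and 3rd days after the operation". The exclusion criteria remove "High perioperative troponin levels due to nonischaemic causes (e.g., sepsis, pulmonary embolism, arrhythmia" and similar cases; they set no preoperative cut-off.

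On the link with the exposure, the Introduction says: "Frail populations often have a greater incidence of subclinical changes in cardiac structure and function". The 11-item modified frailty index (mFI) under Study implementation counts heart failure, myocardial infarction, and angina, coronary intervention or cardiac surgery.

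**The concern.** Two of the four wordings are absolute thresholds. The other two speak of an increase without saying relative to what. The preoperative value would settle the difference, yet no part of the article uses it: there is no required change from baseline, and no separate handling of patients who start at or above 0.03 ng/mL.

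Take a patient at 0.04 ng/mL before and after surgery, with no sepsis, embolism or myocarditis. The threshold is met, and the listed nonischaemic causes are absent. Such a patient is a prevalent case, but can enter the analysis as an incident one at the first postoperative sample. The choice between a 3-day and a 30-day window does not change that. The planned Kaplan–Meier, log-rank and Cox analyses of MINS also presume that patients are event-free at the start.

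If prevalent elevation were equally common in both groups, the main damage would be to the incidence estimate. If it is commoner in frail patients, the misclassification differs by exposure and can produce a frailty–MINS association without any difference in surgical injury. Covariate adjustment would not readily repair this, because the error lies in the outcome and cardiac history is part of the exposure.

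**Working it through.** **1. The plan's own figure.** Inputs from Sample size calculation: 15% frail, 5% non-frail, two-sided α = 0.05, the stated 90% read as power, and allocation k = 570/114 = 5.

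- Pooled proportion: (0.15 + 5 × 0.05)/6 = 0.0667.
- n = [1.960 × √(0.0667 × 0.9333 × 1.2) + 1.282 × √(0.1275 + 0.0475/5)]² / 0.10² = (0.5356 + 0.4743)² / 0.01 ≈ 102.
- With continuity correction: (102/4) × [1 + √(1 + 2 × 6/(102 × 5 × 0.10))]² ≈ 113.7, so 114 frail and 5 × 114 = 570 non-frail.
- Dropout: 114/0.8 = 142.5 → 143; 570/0.8 = 712.5 → 713; total 856.

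The stated sizes reproduce exactly. The point does not rest on an arithmetic error.

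**2. Apparent incidence with no true difference.** Let c be the share with preoperative cTnT ≥ 0.03 ng/mL and t the risk of new injury among the rest. If every such patient is counted, apparent MINS = c + (1 − c) × t. The article gives no value for c, so the values below are assumptions; t = 5% in both groups. Example: frail 0.05 + 0.95 × 0.05 = 9.75%; non-frail 0.01 + 0.99 × 0.05 = 5.95%.

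The rejection probability sums the exact binomial probabilities of all outcome pairs at 114 and 570 for which the uncorrected two-sided chi-square test gives P < 0.05.

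| c frail / non-frail | Apparent MINS | Risk ratio | False rejection |
|---|---|---|---|
| 0 / 0 | 5.0% v 5.0% | 1.00 | 4.7% |
| 2% / 1% | 6.9% v 5.95% | 1.16 | 8% |
| 5% / 2% | 9.75% v 6.9% | 1.41 | 21% |
| 5% / 1% | 9.75% v 5.95% | 1.64 | 33% |
| 10% / 2% | 14.5% v 6.9% | 2.10 | 73% |

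Each row with c above zero is an upper bound, because it assumes that the ischaemia judgement removes no case.

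**3. What a baseline-based definition would do to power.** If the planned 15% v 5% already include prevalent elevation, new injury among the rest is (p − c)/(1 − c).

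| c frail / non-frail | New injury | Power at 114/570 |
|---|---|---|
| 0 / 0 | 15.0% v 5.0% | 93% |
| 2% / 1% | 13.3% v 4.0% | 93% |
| 5% / 2% | 10.5% v 3.1% | 89% |
| 5% / 1% | 10.5% v 4.0% | 76% |
| 10% / 2% | 5.6% v 3.1% | 29% |

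These powers keep the full group sizes and are slightly optimistic if patients with preoperative elevation are left out.

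**4. Tie to the exposure.** One mFI item is 1/11 = 0.09, two are 0.18 and three are 0.27. The top category starts at 0.21, so three items are needed. The three cardiac items alone suffice, but so do diabetes, COPD and treated hypertension.

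**The case against.** A reader might infer that the plan directs chronic elevation to be counted as new injury, and that it therefore inflates MINS in frail patients. The text does not go that far. The event must be judged ischaemic, the listed nonischaemic causes are examples and not a closed list, the diagnostic criteria ask for an increased postoperative level, and nonischaemic elevation is an exclusion. An adjudicator reading these together could reject the patient at 0.04 ng/mL before and after surgery. Supplemental Appendix 1, cited within the outcome definition, is not shown and may say more. So the supportable statement is that nothing shown uses the preoperative value, and that such a case can be counted.

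The size is also open. No prevalence of preoperative elevation is given for either group. The larger false-rejection figures need a fivefold contrast between groups; at 2%/1% the effect is small. The link to the exposure is an inference, and a patient can reach the top mFI category with no cardiac history.

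What remains is that none of these safeguards refers to the preoperative value. The named causes are sepsis, embolism, myocarditis and arrhythmia; stable chronic elevation is not among them. The Abstract's wording omits the judgement altogether. This is not detail left to an analysis plan: the article itself fixes the primary outcome, and does so in wordings that do not agree.

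**Conclusion.** The concern holds as a risk of bias in a stated rule. The outcome is an absolute threshold in two places and an increase in two others, and the scheduled preoperative sample has no stated role. A patient with unchanged preoperative elevation can be counted as MINS unless the ischaemia judgement removes the case.

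A bias towards a frailty–MINS association is plausible on the article's own reasoning but is not demonstrated. Under the assumed prevalences, with no true difference, false rejection runs from about 8% to 73% against a nominal 5%. It stays near nominal if preoperative elevation is rare or balanced between groups. The article does not support the claim that frail incidence is inflated by any particular amount.

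**What to change.** 1. Reconcile the Abstract, the Introduction, the diagnostic criteria and the Primary outcome section, and state how the preoperative cTnT value enters the outcome.
2. Report the share of patients with preoperative cTnT ≥ 0.03 ng/mL by frailty group. This shows directly whether the problem is material.
3. Pre-specify an analysis of new MINS (postoperative ≥ 0.03 ng/mL with preoperative < 0.03 ng/mL) beside the absolute-threshold analysis, either as the primary definition or at least as a key sensitivity analysis.
4. In that analysis, treat patients already ≥ 0.03 ng/mL as not at risk of a new threshold crossing, or apply a rise criterion whose size is fixed before the data are analysed.
5. Flag patients without a preoperative sample, for example emergency cases with deferred consent, and state how they are handled.

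No extra sampling is needed, but the cost is more than analysis-plan wording. It is a protocol-level clarification of the primary outcome in a registered study that began in January 2023. The loss of events could be large. In the 10%/2% scenario with 5% new injury, frail events fall from 0.145 × 114 = 16.5 to 0.90 × 0.05 × 114 = 5.1. If the planned rates include prevalent cases, power could fall to about 29%. Some patients will have no baseline value. If the sponsor prefers to keep the absolute threshold as primary, items 1 to 3 can still be met with the new-MINS analysis as a key sensitivity analysis.

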**Secondary outcome**

b)Intraoperative haemodynamic instability and treatment times will also be recorded (Supplemental Appendix 2).c)All-cause mortality within 30 days after the operation (vascular or nonvascular; definitions are provided in Supplemental Appendix 3).d)Length of stay.e)Quality of Recovery-15 (QoR-15).f)Any complications occurred within 30 days after the operation (Supplemental Appendix 4).g)Readmission to the hospital. (Table 2)

**Table 2 Tab2:** Study assessment procedures and timetable

	STUDY PERIOD					
	Enrolment	Allocation	Postoperation			Close-out
TIMEPOINT	***-D1***	**0**	***D1***	***D2***	***D3***	***D30***
ENROLMENT						
Eligibility screen	X					
Informed consent	X					
Allocation		X				
ASSESSMENTS						
MMSE	X					
BI	X					
mFI	X					
aCCI	X					
Primary outcome						
MINS		X	X	X	X	X
Secondary outcomes						
QoR-15			X	X	X	
Postoperative complications			X	X	X	X
30-day all-cause mortality			X	X	X	X
30-day readmission			X	X	X	X

MMSE, Mini-Mental State Examination; BI, Barthel Index; mFI, modified frailty index; aCCI, age-adjusted Charlson Comorbidity Index; QoR-15, Quality of Recovery-15.

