## Discussion

Identifying, treating and preventing frailty has been a major challenge in the field of geriatrics. Due to its multidimensional nature, frailty not only is a strong risk factor for death but also profoundly affects the response, effectiveness and tolerance to drugs and surgical treatment and has a negative impact on quality of life [32–34]. Cardiovascular disease (CVD) is the main cause of death and hospitalization, especially for the geriatric population [18]. Frailty may be preventable, but when it occurs in the stages before death, it may be irreversible. Therefore, strategies to prevent and slow the progression of frailty are crucial [32, 35]. There is an urgent need to study the clinical characteristics, predictive factors and postoperative outcomes of myocardial injury in geriatric frail patients after noncardiac surgery. We will achieve this main purpose through this prospective, multicentre, cohort study.

Due to the use of anaesthetic, sedative and analgesic drugs, perioperative patients may not experience ischaemic symptoms, which leads to failure to identify MINS and postoperative myocardial infarction. Therefore, monitoring hs-cTnT levels during the perioperative period is highly important for identifying the risk of MINS [36]. In 2014, the European Society of Cardiology and the European Society of Anaesthesiology (ESC/ESA) released guidelines that explicitly recommended the clinical use of risk indicators, including myocardial markers, for preoperative risk stratification of patients, and for high-risk patients, cTn detection can be considered before major surgery and within 48–72 h after surgery [6]. The guidelines issued by the Canadian Cardiovascular Society (CCS) in 2017 also recommended that the level of cTn in noncardiac patients be monitored dynamically within 48–72 h after surgery to strengthen the assessment of patients’ perioperative cardiac risk [7]. We hope to clarify the clinical significance of routine detection of cTn levels in geriatric frail patients older than 65 years of age during the perioperative period.

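### QoR-15 has no scheduled preoperative score, so a frail versus non-frail difference on D1 to D3 cannot be split into starting level and recovery

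*Protocol article*

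**What the plan says.** The protocol article's list of secondary outcomes names "e)Quality of Recovery-15 (QoR-15") without a time point, a change score or a reference value. Table 2 marks it on D1, D2 and D3; its -D1 and day 0 cells are empty. The same table puts MMSE, BI, mFI and aCCI on -D1.

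The Study implementation section describes the instrument as a "patient-reported outcome measurement validated to measure the QoR after surgery and general anaesthesia". The score "ranges from 0 to 150, with a higher score indicating better recovery". (The subject of that sentence is printed as BDI, but it stands in the QoR-15 paragraph.) Results are graded in absolute bands: "The following QoR scoring criteria will be used: excellent (QoR-15 > 135"), then good from 122 to 135, moderate from 90 to 121, and poor below 90.

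The exposure is "Preoperative frailty in geriatric patients", measured by an 11-item index in which a BI of 60 or less counts as one positive item. The Discussion says that frailty "has a negative impact on quality of life". The Statistical analysis section names no test for QoR-15.

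**The concern.** In a randomised comparison the groups have the same expected starting level, so a score taken only after surgery can still be compared fairly. Here the groups are selected on preoperative health, and the protocol's own account of frailty gives reason to expect that patient-reported state differs between them before the operation. A low D1 score in a frail patient may then mean poor recovery or simply that patient's usual state.

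The absolute bands do not help. A patient who scored 120 before surgery and is back at 120 on D3 is graded moderate despite a complete return to the starting level.

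At stake is how this secondary outcome can be read. A group difference could be reported as worse recovery in frail patients when part or all of it was there beforehand. The timing of data collection is fixed by the protocol, and an analysis plan cannot supply a measurement that was never taken.

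**Working it through.** **1. Group sizes.** The protocol gives no figure for QoR-15, so the planned evaluable numbers are used, after checking that they reproduce. Inputs from Sample size calculation: MINS 15% versus 5%, two-sided α 0.05, the stated 90% read as power, and a 5:1 ratio.
- Pooled rate: (0.15 + 5 × 0.05)/6 = 0.0667.
- Uncorrected frail n: [1.960 × √(1.2 × 0.0667 × 0.9333) + 1.282 × √(0.15 × 0.85 + 0.05 × 0.95/5)]² / 0.10² = 102.
- With continuity correction: (102/4) × [1 + √(1 + 12/(5 × 102 × 0.10))]² = 113.7, so 114 frail and 5 × 114 = 570 non-frail.
- With 20% loss: 114/0.8 = 142.5, rounded up to 143; 570/0.8 = 712.5, rounded up to 713; total 856.

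The plan's figures reproduce. The point does not depend on them, but they set the scale of the illustration.

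**2. What a comparison after surgery estimates.** Let g be the preoperative gap between groups and d the difference in perioperative change. The D1 difference estimates g + d. With a -D1 score, the difference in change estimates d alone. Without it, g and d cannot be separated.

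**3. Illustration with d = 0.** The gap and the SD are assumptions, since the documents give neither. For a gap of 5 and SD 20:
- SE = 20 × √(1/570 + 1/114) = 2.05.
- z = 5/2.05 = 2.44.
- Chance of p < 0.05 ≈ Φ(2.44 − 1.96) = 68%.

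Over a range of assumptions:

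| Assumed gap | SD 15 | SD 20 | SD 25 |
|---|---|---|---|
| 3 points | 50% | 31% | 22% |
| 5 points | 90% | 68% | 50% |
| 8 points | >99% | 97% | 88% |

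In the same scenario, a comparison of change from -D1 has expected difference 0 and rejects at the nominal 5%. Adjusting for baseline by ANCOVA would remove only part of the gap in non-randomised groups, leaving (1 − slope) × g.

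**4. Size against the bands.** Good spans 135 − 122 + 1 = 14 points; moderate spans 121 − 90 + 1 = 32. A 5-point gap is about a third of the first (5/14 = 36%) and a sixth of the second (5/32 = 16%).

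**5. Whether another measure fills the gap.** BI, MMSE and aCCI are scheduled on -D1 and allow partial adjustment. None is a patient-reported recovery score, and BI feeds the exposure itself. EQ-5D-3L is in the staff training ("correctly administer the MMSE, aCCI, mFI, BI, EQ-5D-3 L, and QoR15") but has no row in Table 2.

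**The case against.** Absolute status after surgery is a legitimate outcome, and the protocol describes and grades QoR-15 in just that way. No QoR-15 test is written down, so the group comparison is implied by its place as a secondary outcome of a two-group cohort. A lower usual state may also be part of what frailty means rather than a bias to subtract. This stands. It means that the outcome is not invalid, but that it must be described as status unless a baseline is taken.

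A reader might infer that frail patients are bound to show worse recovery. The documents do not support that. They give no starting gap, the quality-of-life remark is general background, and the index is mostly disease history. A patient with diabetes, treated hypertension and a past myocardial infarction scores 3/11 = 0.27, above the 0.21 cut-off, with a BI of 100. Nor is a shift of a full band supported. That would need both a gap of about 14 points, for which there is no source, and the 14-point band rather than the 32-point one.

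Table 2 is also incomplete in other places. Blood sampling before surgery is required in the text but MINS is not marked on -D1, and length of stay has no row. The 24 preoperative variables are in Supplemental Appendix 5, which is not shown, so some patient-reported baseline measure may exist there. QoR-15 does have its own row, however, with three marked days and an empty -D1 cell.

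Finally, relying on change alone would drop patients who consent after surgery. The Introduction cites frailty of 53% in emergency hip fracture surgery against 23% in elective orthopaedics, so those dropped may more often be frail. This stands and shapes the fix.

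**Conclusion.** The point holds as a limit on interpretation. With QoR-15 scheduled on D1 to D3 only and groups formed by preoperative frailty, a group difference cannot be attributed to recovery as distinct from starting level. Its direction and size are unknown. The 68% figure, and the range from 22% to over 99%, rest wholly on assumed gaps of 3 to 8 points, SDs of 15 to 25, identical change in both groups, and 570 versus 114 evaluable patients. They show that a modest gap could be enough to produce significance, not that one exists. It is a cheap improvement to one secondary outcome. The missing EQ-5D-3L visit is a separate scheduling point.

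**What to change.** - Add QoR-15 to the -D1 column of Table 2 for patients who consent before surgery, in the session that already holds BI and MMSE.
- Report the D1 to D3 group comparison in two ways: absolute postoperative score in all patients, and change from -D1 in patients with a baseline. Show the number without a baseline by group.
- For patients without a baseline, describe QoR-15 as postoperative status, not as recovery attributable to surgery.

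The cost is a few minutes per patient and one more entry on the case report form. The protocol itself says that "the QoR-15 is more practical to use because it is shorter and takes less time to complete" (compared with the QoR-40). Baselines will be missing in emergency and deferred-consent patients, and in everyone enrolled since January 2023 before the change. Where recruitment is already complete, only the wording of the report can still be changed.
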